## **2. OBJECTIVES**

The objective of this study is to investigate whether Parkinson's patients in the *off* phase are capable to use a dry powder inhaler correctly, regarding the generation of an appropriate inhalation curve for aerosol generation and transport into the peripheral airways.

For the Twincer™ to be suitable for Parkinson's patients in the *off* period, it has to be known at which inspiratory air flow and inhaled volume the fine particle dose has to be delivered.

This may require adjustment of emission time for the fine particle dose and air flow resistance of the inhaler device. The data obtained with the test inhaler (by using 3 resistances) could be used to optimise the Twincer™ DPI for Parkinson's patients. Specific characteristics of the Twincer™ could be adjusted to what Parkinson's patients can do with a DPI, in order to realise a DPI with levodopa that Parkinson's patients can operate during the *off* phase. Such characteristics are for example the resistance, the dose and the emission profile. With this new knowledge we aim to develop a DPI with levodopa for Parkinson's patients.

**Primary Objective:** to determine if a Parkinson's patient can operate a test inhaler correctly during *off* periods. The parameter that describes whether or not a Parkinson's patient is capable of using the inhaler correctly is the pressure drop (s)he creates over the inhaler upon inhalation (by testing 3 resistances, of which one is comparable with Twincer™, one higher and lower). From the created pressure drop, various inspiratory parameters can be calculated. For the Twincer™ a pressure drop between 2 kPa and 4 kPa is optimal.

### 3. STUDY DESIGN

The study is a non-therapeutic observational study in which the applicability of dry powder inhalation in Parkinson's patients will be investigated. The study will be conducted with an instrumented test inhaler. The test inhaler concept is a dummy, without any drug substance or excipient. It is equipped with a pressure drop meter to record the inhalation curve of the patient. A more extensive description of the test inhaler is given in the introduction and in paragraph 5.2 *Test inhaler*.

The duration of the study is approximately 12 months (different days) and will be conducted at the Martini Ziekenhuis. Only Parkinson's patients who are under treatment by a neurologist in the Martini Ziekenhuis are able to join. For the individual patient, the test will last maximally 30 minutes (including instruction and motor function examination). The tests will be performed in the Martini Ziekenhuis.

A family member is allowed to be present during the tests. In order to be able to measure during an *off* period, patients will be asked to postpone a dose of levodopa until they become *off*. As soon as the patient starts feeling *off*, explanation of the test procedure will be started. Because becoming *off* is not one fixed point in time but will take a while, a 15 minute waiting period before start of the inhalation test will be taken. During this waiting period, the researcher will explain the test procedure. The patient will receive instructions on how to use the test inhaler. The instructions will be given orally and partly be demonstrated by the instructor, partly be visualised by photographs and recordings of generated flow curves on a computer screen. 15 minutes after the patients started to feel *off*, the motor examination will be performed. We prefer to start the inhalation tests when the UPDRS III motor score is at least 30 (out of 56). However, if the patient does not reach a UPDRS III motor score of 30 after a 2 hour waiting time, inhalations tests will start if the UPDRS III motor score is at least 25. The patient will do a couple of inhalations with three different resistances. After the patient finished the test inhalations, the patient will take his/her levodopa. The patient will leave the hospital only in an *on* period.

All patients will receive the opportunity to do a few test inhalations with the standard test inhaler. During the inhalations the patient can see the flow curves on the computer screen. This gives the opportunity to illustrate and explain how the inhalation manoeuvre can be improved. The data that will be collected per Parkinson's patient consist of a maximum of ten flow curves (for the three resistances together).

## **4. STUDY POPULATION**

### **4.1 Population (base)**

The study will be conducted in 15 Parkinson's patients. The duration of the study is approximately 12 months and will be conducted at the Martini Ziekenhuis. The patients are aged 18 year and older and do have recognizable *off* periods. Informed consent of the patient will be obtained prior to participation. Parkinson's patients with active pulmonary disease are excluded. Patients currently treated with apomorphine or duodopa by pump are also excluded.

### **4.2 Inclusion criteria (must meet all inclusion criteria)**

- Predictable *off* periods.
- Recognizable *off* periods for themselves and others.
- At least 2 years of levodopa use.
- Signed informed consent.
- Diagnosed with Parkinson's disease according to the UK Parkinson's disease society Brain Bank Clinical Diagnostic Criteria.

### **4.3 Exclusion criteria (excluded if they meet one or more of the following criteria)**

- Cognitive dysfunction, which precludes good understanding of instructions and/or informed consent.
- Current treatment with apomorphine or duodopa by pump.
- Active pulmonary disease.

### **4.4 Sample size calculation**

The study is an observational study designed to obtain insight into the ability of Parkinson's patients to use a dry powder inhaler during *off* periods.

We based our sample size calculation on previous studies performed in Parkinson's disease. Canning et al (1997) evaluated exercise capacity, respiratory function and gait in 16 patients with mild to moderate Parkinson's disease. Guedes et al (2012) investigated the MIP and MEP in 26 patients with Parkinson's disease during *on* and *off* periods of levodopa compared to healthy volunteers. Seccombe et al (2011) recruited 19 patients with mild-moderate Parkinson's disease without respiratory disease and assessed ventilatory control. Since we only want to obtain insight into the ability of Parkinson's patients to use a dry powder inhaler during *off* periods, 15 patients valid for evaluation is sufficient.

## 5. METHODS

### 5.1 Study parameters

#### 5.1.1 Main study parameters

The main study parameter is to determine if a Parkinson's patient can operate a test inhaler correctly during *off* periods, by testing if they can generate a sufficiently large airflow and volume through the test inhaler *theoretically* necessary to disperse a medicinal powder and transport the aerosol into the lower airways during an *off* period.

The parameter that describes whether or not a patient is capable of using the inhaler correctly is the (duration of the) pressure drop (s)he creates over the inhaler upon inhalation. For the Twincer™ a pressure drop between 2 kPa and 4 kPa is optimal. The main study parameter therefore is the capability of patients to create a pressure drop between 2 kPa and 4 kPa by using a test inhaler with the resistance comparable with the Twincer™. At least 11 out of 15 patients should be able to create a pressure drop between 2kPa and 4 kPa, when using the resistance comparable of the Twincer™.

From the pressure drops created with the three resistances, the following parameters (which give more insight in the inhalation profile) will be calculated:

- Peak and mean inspiratory flow rate (PIFR and MIFR).
- Acceleration towards peak inspiratory flow rate (flow increase rate: FIR).
- Inhaled volume.
- Total inhalation time.

The data obtained with the test inhaler (by using the three resistances) could be used to optimise the Twincer™ DPI for Parkinson's patients. Specific characteristics of the Twincer™ could be adjusted to what Parkinson's patients can do with a DPI, in order to realise a DPI with levodopa that Parkinson's patients can operate during the *off* phase. Such characteristics are for example the resistance, the dose and the emission profile. With this new knowledge we aim to develop a DPI with levodopa for Parkinson's patients.

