**SUMMARY**

**Rationale:** because of limited treatment options with a very rapid onset for Parkinson's disease patients in the *off* period, there is a need for the development of rapid onset options to administrate levodopa, like a pulmonary formulation of levodopa.

The development of a dry powder inhaler (DPI) that suits the needs of Parkinson's patients, based on their inspiratory capacities, is essential. In this study, we will investigate the applicability of dry powder inhalation in Parkinson's patients in order to enable us to develop a DPI specifically for this patient group.

**Objective:** to determine if a Parkinson's patient can operate a test inhaler correctly during *off* periods, by testing if they can generate a sufficiently large airflow and volume through the test inhaler *theoretically* necessary to disperse a medicinal powder and transport the aerosol into the lower airways during an *off* period.

**Study design:** non-therapeutic observational study.

**Study population:** 15 Parkinson's patients.

**Main study parameters:** the main study parameter is the ability of a Parkinson's patient to use the inhaler correctly during *off* periods. The parameter that describes whether or not a Parkinson's patient is capable of using the inhaler correctly is the inspiratory flow curve (s)he generates through the inhaler upon inhalation, from which various inspiratory parameters relevant to dispersion and deposition can be calculated. For good performance of the current Twincer™, a single use dry powder inhaler in development for levodopa, a pressure drop between 2 and 4 kPa and a total inhalation time of 1 to 1.5 s are optimal, but, depending on the performance of the patients in this study further optimisation of the inhaler design is possible.

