### 1.3 The Twincer™ DPI

The Twincer™ DPI is designed to deliver high doses of drugs. It has been developed by the department of Pharmaceutical Technology and Biopharmacy of the University of Groningen. The Twincer™ has an efficient dispersion principle, based on patented air classifier technology, which can generate high dosages of the medication. This reduces the number of inhalations to one or maximally two with a total administration time of less than a minute including preparation of the inhaler. It also enables a reduction of the influence of the patient's breathing behaviour on drug delivery. The Twincer™ is ready-to-use, the only action the patient (or his/her caregiver) has to undertake is pulling the foil strip from the blister. The Twincer™ also has a conveniently small size of about a credit card. Finally, the Twincer™ is a disposable device. In figure 1, a prototype of the Twincer™ is shown (de Boer et al., 2006).

[figure not shown]

*Figure 1: Injection moulded prototype of the Twincer™ DPI*

However, the Twincer™, like nearly all currently marketed dry powder inhalers, is a passive device. This means that the energy for the emptying of the dose compartment (entrainment of the powder) and dispersion of the powder into the correct aerodynamic particle size distribution is derived from the inhaled air stream. To deliver sufficient energy for that, it requires that the air flow rate through the inhaler is sufficiently high.

Additionally, the inhaled volume has to be sufficiently large for convective transport of the aerosol into the peripheral airways and a certain breath hold period after inhalation (preferably 5 s) is needed to give 1-3 µm particles sufficient time for sedimentation in the smallest airways. Dry powder doses with the Twincer™ are preferably (but not necessarily) administered in one single inhalation manoeuvre. To decide whether the Twincer™ is suitable for Parkinson's patients in the *off* period, it has to be investigated whether these patients can comply with the requirements for good inhalation through this device. If not, adjustment of the dispersion efficacy and emission time for the fine particle dose as well as the air flow resistance of the inhaler device may be needed.

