In this study, an accredited UPDRS scorer will rate the UPDRS III motor section for each patient, immediately before the inhalation tests will start. This allows the researchers to specify the motor function during inhalation. We prefer to start the inhalation tests when the UPDRS III motor score is at least 30 (severe Parkinson). However, if the patient does not reach a UPDRS III motor score of 30 after a 2 hour waiting time, inhalations tests will start if the UPDRS III motor score is at least 25.

*Test 2: Recording of the inhalation curve through the test inhaler with standard mouthpiece and (medium) air flow resistance*

The patient will be instructed to first breath out completely (turning the face away from the test inhaler) and then breath in firmly and as long as possible through the test inhaler. Additionally, the patient will be asked to hold the breath for at least 3 to 5 s (if possible). A few inhalations will be practiced before recording of the first curve (and breath hold period) during which the patient can see the flow curve of his/her performance on the computer screen. This gives the opportunity to explain and illustrate how the inhalation manoeuvre can be improved.

When the patient has finished all his/her inhalations (maximum of 10 inhalations; excluding practicing before recording will start), the test inhaler and the mouthpiece that were used will be cleaned and disinfected with ethanol and be allowed to dry prior to using them for the next patient.

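### The 11-of-15 success rule counts pressure drop alone, so meeting it shows ability to disperse the powder, not the transport to the lower airways that the objective also asks for

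*Protocol*

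**What the plan says.** **What correct use means.** The Summary and section 5.1.1 say the study determines whether a patient in the *off* state can operate the inhaler correctly "by testing if they can generate a sufficiently large airflow and volume through the test inhaler", as needed in theory both to disperse a powder and to bring the aerosol into the lower airways. Section 1.3 states the transport side as a requirement: "the inhaled volume has to be sufficiently large for convective transport of the aerosol into the peripheral airways". It adds a second condition, so that fine particles have time to settle: "a certain breath hold period after inhalation (preferably 5 s) is needed".

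**Which parameter describes it.** In the Summary's paragraph on the main parameter, "a pressure drop between 2 and 4 kPa and a total inhalation time of 1 to 1.5 s are optimal" for the current Twincer. In section 5.1.1 the describing parameter "is the (duration of the) pressure drop (s)he creates over the inhaler upon inhalation". Section 2 names pressure drop only. Section 5.2 speaks of a peak pressure drop and links the 2 to 4 kPa range to breaking up the powder.

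**What decides success.** Section 5.1.1 continues: "The main study parameter therefore is the capability of patients to create a pressure drop between 2 kPa and 4 kPa", at the Twincer-like resistance, and then "At least 11 out of 15 patients should be able to create a pressure drop between 2kPa and 4 kPa". No other numeric criterion exists. Inhaled volume and total inhalation time are calculated as further information on the profile, without limits. Section 7.1 describes only the pressure-drop capability, qualitatively.

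**What patients are told.** Under Test 2 in section 5.3 they exhale fully, "then breath in firmly and as long as possible through the test inhaler", and hold the breath for 3 to 5 s if they can.

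**The concern.** The objective has two parts, dispersion and transport. The success rule measures only the first. Within section 5.1.1 volume stands in the opening definition and is absent from the rule; duration is mentioned in parentheses and then given no limit. A patient whose curve reaches 2 kPa briefly and then collapses is counted the same way as one who sustains the manoeuvre.

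If 11 or more patients pass, the natural report would be that Parkinson's patients can use the inhaler correctly in the *off* state. The rule does not carry that statement. The result is meant to steer the resistance and emission profile of the device, so it matters which of the two abilities has been shown.

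This is not a detail left for a statistical analysis plan: the protocol itself fixes both the rule and the threshold, and fixes them more narrowly than its own objective.

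**Working it through.** **The plan's own figure.** 11/15 = 73.3%. The protocol gives no error rate, power, null rate or target rate, so neither the threshold nor the sample size of 15 can be reproduced. The check concerns what the rule measures.

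**Step 1: set the texts side by side.**

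| Place | Pressure drop | Inhalation time | Volume | Breath hold |
|---|---|---|---|---|
| Summary, objective | (airflow) | – | yes, no figure | – |
| Summary, main parameter | 2–4 kPa, optimal | 1–1.5 s, optimal | – | – |
| 1.3 | (flow rate must be high enough) | – | required, no figure | needed, preferably 5 s |
| 2, primary objective | 2–4 kPa, optimal | – | – | – |
| 5.1.1, definition | (airflow) | duration in parentheses, no limit | yes, no figure | – |
| 5.1.1, success rule | 2–4 kPa in at least 11 of 15 | – | – | – |
| 5.2 | peak of 2–4 kPa, for break-up | derived, no limit | derived, no limit | – |

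The success rule carries one column only.

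**Step 2: how much volume can differ between two passing curves.** Inputs from Appendix 1: √dP = flow × R, and 45 to 110 L/min at 4 kPa across marketed inhalers. The Twincer's own resistance is not given, so both ends of that range are carried. Assumptions of this check: flow rises and falls linearly (a triangle), peaks at 2 kPa, and lasts 0.5 s.

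- Flow at 2 kPa = flow at 4 kPa × √(2/4): 45 × 0.707 = 31.8 L/min (high resistance); 110 × 0.707 = 77.8 L/min (low resistance).
- Volume of a triangle = ½ × (flow/60) × time.

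| Time | High resistance | Low resistance |
|---|---|---|
| 0.5 s | ½ × 0.530 × 0.5 = 0.13 L | ½ × 1.296 × 0.5 = 0.32 L |
| 1.0 s | 0.27 L | 0.65 L |
| 1.5 s | 0.40 L | 0.97 L |

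With shape and peak held equal, volume is proportional to time: 0.5/1.0 = one half and 0.5/1.5 = one third. All six curves reach a peak of 2 kPa and all six pass.

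**Step 3: could a joint criterion change the count?** The protocol gives no rates, so these are assumptions. Let p be the share of patients who reach the pressure range, and q the share of those who also meet a time criterion. The chance of at least 11 of 15 is the upper binomial tail at p × q.

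| p | q = 1 (pressure only) | q = 0.9 | q = 0.8 | q = 0.7 |
|---|---|---|---|---|
| 0.8 | 0.836 | 0.585 | 0.322 | 0.137 |
| 0.9 | 0.987 | 0.861 | 0.585 | 0.294 |

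If nearly all who reach the pressure also sustain the inhalation, the two counts agree. If a fifth do not, they can fall on different sides of 11.

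**The case against.** **Pressure drop is a reasoned choice.** Section 2 names it as the describing parameter, and Appendix 1 argues that enough pressure drop, rather than enough flow rate, is what correct operation depends on. This stands as a reason to keep the pressure count. It answers only half of the point, because Appendix 1 contrasts pressure with flow rate, not with volume or duration.

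**Volume is something the study sets out to learn.** Section 2 says the flow and volume at which the dose must be delivered have to be found out, and the Summary leaves the device open to redesign. This stands. A reader might infer that the protocol forgot a volume limit and needs one in its success rule. The documents do not support that: they give no volume figure, and a cut-off set without justification would presuppose part of the answer.

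**Time and breath hold are not ignored.** Duration is named in section 5.1.1, inhalation time and volume will be calculated, and the wording of Test 2 implies that the breath hold is recorded. It would be wrong to infer that these data go uncollected. Without a limit, however, none of them can alter the 11-of-15 result.

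**The 1 to 1.5 s range is called optimal, not required.** True, but the 2 to 4 kPa range is called optimal in the same sentence, and it became the criterion.

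**Short inhalations may be rare.** Patients are told to inhale as long as possible, after practice with on-screen feedback, and active pulmonary disease is an exclusion. A reader might infer that *off*-state patients are likely to give brief, small inhalations. Nothing in the protocol shows this; section 1.4 cites reduced maximal respiratory pressures, not short or small breaths. Equally, an instruction does not show that patients could follow it, and that ability is what is being tested.

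**The study only seeks insight.** No hypothesis test or treatment decision hangs on 11 of 15. This limits the consequence but does not make the rule match the objective.

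**Conclusion.** The point holds as a mismatch between objective and success rule. Meeting 11 of 15 would show that patients can produce the pressure drop linked to dispersion. It would not show the volume or duration linked to transport, which the protocol counts as part of correct use.

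The size is illustrative. With a triangular 0.5 s inhalation peaking at 2 kPa and the Appendix 1 device range, a passing curve can carry 0.13 to 0.32 L, one third to one half of the volume of the same shape over 1 to 1.5 s. Duration and shape are assumptions, as is reading the rule as a peak, which follows section 5.2. A larger gap could be produced by comparing a triangular puff with an inhalation held at constant pressure, but part of that gap would come from the change of shape, so it should not be used.

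How often the pressure-only and joint counts would differ cannot be known from the protocol. The point deserves a change because the study's conclusion depends on it and the data are already being collected.

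**What to change.** 1. Reconcile the Summary, section 2, section 5.1.1 and section 5.2 so that they name one deciding parameter, and say whether it is a peak or a sustained pressure drop.
2. At the Twincer-like resistance, count the patients who meet the pressure-drop criterion and a total inhalation time of at least 1 s on one and the same curve. Report this count beside the pressure-only count. The 1 s figure is the lower end of the Summary's optimal range; making it a criterion is a choice that the protocol should state.
3. Use 1.5 s descriptively only, since an upper limit conflicts with the instruction to inhale as long as possible.
4. Report inhaled volume for the same curves, with no pass/fail limit unless the device team can justify one before the first patient. Report the breath-hold times, including how many patients reach the 3 to 5 s requested.
5. State that the pressure-only 11-of-15 result supports a conclusion on dispersion, not on transport to the lower airways.

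The cost is protocol wording and one further tabulation; the recorded curves already yield time and volume, and no procedure is added. The downside is that the joint rate can be no higher than the pressure-only rate, and may look less favourable.

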## 5.2 Test inhaler

The study will be conducted with an instrumented test inhaler with exchangeable air flow resistances. The test inhaler is a dummy, without any drug substance or excipient. The device is provided with a pressure drop meter that records the pressure drop that is generated when the patient inhales through it. The pressure drop meter is linked to a computer equipped with software that calculates from the pressure drop the inspiratory flow rate as function of the inhalation time. Various relevant parameters can be derived from this curve, such as inhaled volume, total inhalation time and mean and peak inspiratory flow rate. In order to adequately break up (disperse) the inhalation powder with the current TwincerTM into particles in a size range suitable for lung deposition, a peak pressure drop within the range of 2 to 4 kPa must be generated. Because the test inhaler can mimic the resistance of the current TwincerTM, it can be investigated whether the patients can fulfil this requirement or adjustment of the TwincerTM to the inspiratory capabilities of Parkinson's patients in the off period will be needed. This may depend on the inhaler resistance, and for that reason different resistance values will be tested. The test inhaler is made of polypropylene, a robust and light weight material that does not break, to prevent the formation of inhalable particles (e.g. from dropping, thumping); the exchangeable mouthpiece will be cleaned and disinfected between Parkinson's patients. The design of the test inhaler excludes the inhalation of inhaler parts during the tests. The test inhaler is shown in figure 2 in the introduction. This figure shows that the test inhaler does not resemble the TwincerTM. It is a measuring instrument specially designed for inventory studies regarding inspiratory capacities. The test inhaler has been successfully used in another study; (ChildDPI-1) 'Investigation of the applicability of dry powder inhalation in school children' and has therefore been tested for technical and hygienic safety by the medical technique of the UMCG.

